### Participants

The 166 patients required for the non-inferiority RCT will have to meet the same inclusion criteria as in the TREFAMS-CBT study [13, 26, 27]: (a) definitive diagnosis of MS, (b) severely fatigued, (c) age of between 18 and 70, (d) ambulatory, (e) no evident signs of an exacerbation and no corticosteroid treatment in the past 3 months, (f) no current infections, (g) no anaemia, and (h) a normal thyroid function. The exclusion criteria are (a) depression, (b) primary sleep disorders, (c) other severe somatic or psychiatric co-morbidity, (d) current pregnancy or having given birth in the past 3 months, (e) pharmacological treatment for fatigue that was started in the past 3 months, (f) non-pharmacological therapies for fatigue that took place in the last 3 months, (g) having received CBT in the TREFAMS trial. This last exclusion criterion is added for this study. See Table 1 for the operationalization of the inclusion and exclusion criteria. As effectiveness of the booster programme can be measured only if patients have completed the initial treatment, the following additional inclusion criteria were defined for participation in the second randomized clinical trial testing the effectiveness of MS Stay Fit: (a) having started treatment (i.e., formulated treatment goals after the first session of CBT or MS Fit); (b) having finished the initial treatment period with a face-to-face session and assessment at T20.

**Table 1 Tab1:** Inclusion and exclusion criteria of the non-inferiority trial

Inclusion criteria	Exclusion criteria
a. Definitive diagnosis of MS confirmed by a neurologist	a. Depression (BDI >4 and meeting criteria of depression as assessed by MINI)
b. Severely fatigued (CIS20r fatigue ≥35)	b. Primary sleep disorders (anamnesis)
c. Age between 18 and 70	c. Severe co-morbidity (CIRS item ≥3)
d. Ambulatory patients (EDSS ≤6)	d. Current pregnancy or having given birth in the past 3 months
e. No evident signs of an exacerbation, or corticosteroid treatment in the past three months	e. Pharmacological treatment for fatigue that was started in the past 3 months
f. No current infections (anamnesis)	f. Non-pharmacological therapies for fatigue that took place in the last 3 months
g. No anaemia (anamnesis)	g. Receiving CBT in the TREFAMS-CBT trial
h. A normal thyroid function (anamnesis)	

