#### Booster trial (RCT 2)

This RCT concerns a superiority between-group comparison at 1-year follow-up of MS Stay Fit (i.e., web-based booster sessions combined with email contact and video consultations versus no booster sessions). Treatment effects on fatigue are assumed to be maintained with additional booster sessions but to gradually wear off to the fatigue level at baseline in the study group without additional booster therapy sessions. In the TREFAMS-CBT study, the treatment effects gradually wore off directly post-treatment until 1 year after the start of treatment [16]. At 1-year follow-up, fatigue levels in the CBT group were comparable to the level of fatigue at baseline. A between-group difference of 6.7 points on CIS20r fatigue is expected. Two-sided significance testing with an α of 5%, two study groups of 75 participants at 1 year, will result in a power of 98%. Therefore, the total number of enrolled patients (two groups of 83, i.e., 75 patients plus a 10% attrition rate) yields sufficient power in RCT 2 to address the second research question.

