#### Primary outcome measure

In both RCTs, the primary outcome measure will be fatigue severity, as measured by the CIS20r fatigue severity subscale, either at the end of initial treatment (RCT 1: T20) or at 1 year (RCT 2: T52). At these time points, the differences in fatigue severity between both groups will be assessed. The same primary outcome measure is used as in the TREFAMS-CBT trial. The CIS20r is a 20-item self-reported questionnaire consisting of four subscales: (a) fatigue severity (eight items), (b) reduction in motivation (four items), (c) reduction in physical activity (three items) and (d) concentration problems (five items) [38, 50]. Items are answered on a 7-point Likert scale and added to a total score. The total score of the fatigue severity subscale can vary between 8 and 56 points. The CIS20r is a reliable and valid instrument for measuring fatigue in various study populations [39]. A cutoff score of 35 or higher is used to discriminate between severe fatigue and fatigue levels within the normal range.

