### Participant retention

Participants receive the questionnaires online. For optimal retention, participants will be contacted by email or phone by the research assistant when they have not started the completion of the questionnaires within 1 week. Randomization is carried out after completing all questionnaires at T0 (R1) or T20 (R2), preventing missing data at these important moments. When participants are not willing to complete all measurements at T20, T39 or T52, they are asked to at least fill in the fatigue subscale of the CIS20r, which the primary outcome measure.

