#### Effectiveness of CBT booster sessions at 52 weeks

Primary analysis of long-term effects of additional booster sessions will be based on ITT using mixed model analysis with CIS20r fatigue severity 1 year after the start of treatment (T52) as dependent measure and condition (booster session vs. no booster sessions) as fixed factor. In case of a large attrition rate, a per-protocol analysis will be added.

To compare the effect of booster sessions on the secondary outcome measures, the ITT mixed model analysis will be repeated with the secondary outcomes at T52 as dependent variable and study group as fixed factor.

In a separate analysis, we will additionally investigate the differential effect of the booster sessions in patients who are no longer severely fatigued at T20 compared with those who are still fatigued at T20.

Analyses of factors mediating long-term effectiveness will be conducted. In addition, analyses will be carried out to identify possible moderators of the response to the booster sessions and response to face-to-face or blended CBT.

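### The additional RCT 2 analysis of who benefits from the booster splits the T20 fatigue score at 35, which loses information and power if the benefit changes gradually with the score

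*Protocol article*

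**What the plan says.** The section on effectiveness of booster sessions at 52 weeks adds, separately from the primary analysis, a search for any "differential effect of the booster sessions in patients who are no longer severely fatigued at T20 compared with those who are still fatigued at T20". The number 35 is not repeated there, but the document defines the term twice: in the eligibility table ("Severely fatigued (CIS20r fatigue ≥35") and under the primary outcome measure ("A cutoff score of 35 or higher is used to discriminate between severe fatigue and fatigue levels within the normal range"). The contrast is therefore T20 score below 35 against 35 or above.

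The score being split is fine-grained: "The total score of the fatigue severity subscale can vary between 8 and 56 points". It is also complete where it is needed: "Randomization is carried out after completing all questionnaires at T0 (R1) or T20 (R2), preventing missing data at these important moments".

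The sample size section for RCT 2 gives the booster hypothesis: "Treatment effects on fatigue are assumed to be maintained with additional booster sessions but to gradually wear off to the fatigue level at baseline"; the wearing off refers to the group without boosters. It adds: "A between-group difference of 6.7 points on CIS20r fatigue is expected". The only power figure concerns the main comparison: "Two-sided significance testing with an α of 5%, two study groups of 75 participants at 1 year, will result in a power of 98" per cent. No power is claimed for the analysis by T20 status.

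**The concern.** The hypothesis is about keeping a gain. Read patient by patient, the booster can protect only what that patient stands to lose, T0 minus T20, and this has no step at 35. Everyone enters at 35 or above. A patient who goes from 36 to 34 has 2 points to lose but counts as no longer severely fatigued. One who goes from 50 to 36 has 14 points to lose but counts as still fatigued. The protocol's own definition of clinically significant improvement accepts an 8-point gain even if the score stays at 35 or above, so the split puts some of its responders with the non-responders.

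An interaction test is usually much weaker than the main comparison. Dichotomising the modifier weakens it further, so a null result could be taken to mean that the booster works equally for everyone. It also hides where along the score the booster helps.

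**Working it through.** **1. The plan's own figure.** No power is stated for this analysis. The 98% for the main comparison cannot be reproduced directly because no SD is given. It requires SD = 6.7 / [(1.960 + 2.054) × √(2/75)] = 6.7 / (4.014 × 0.1633) = 10.2. The article gives no T20 mean, SD or share below 35, so all results below rest on assumptions.

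**2. Information kept by a cut.** This is the squared correlation between the score and its indicator. For a normal score with linear modification and share p below the cut, it equals φ(z_p)² / [p(1 − p)].

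- p = 0.5: 0.3989² / 0.25 = 0.637, a loss of 36.3% (the minimum for a normal score).
- p = 0.4: 0.3863² / 0.24 = 0.622, a loss of 37.8%.
- p = 0.3: a loss of 42.4%. p = 0.2: a loss of 51.0%.

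A test with 80% power on the full score has noncentrality 1.960 + 0.842 = 2.802. At p = 0.5 this becomes 2.802 × √0.637 = 2.236, and Φ(2.236 − 1.960) gives about 61% power.

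**3. Other shapes, cut at 35.** Loss of information:

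- Normal, rounded and bounded to 8-56 (mean 32-38, SD 10-13): 32.5-36.9%.
- Simulated from the booster hypothesis (baseline mean 43, SD 6, truncated at 35; mean gain 6.7-12, SD 8-10.2): 34-37%.
- Uniform: 25-26%.
- Bimodal, responders and non-responders: 18-31%.

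In the hypothesis-based simulations the mean benefit falls smoothly: about 18-20 points at T20 scores 20-24, 10-12 at 30-34, 7-8 at 35-39 and 3-4 at 40-44.

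**4. Interaction power by simulation.** Inputs: 75 per arm (from the article), mean gain 6.7 (the article's expected difference); assumed: baseline N(43, 6) truncated to 35-56, gain SD 8, 10 or 12, error SD 8. With booster, T52 = T20 + e. Without, T52 = T20 + 6.7(1 − k) + k(T0 − T20) + e, where k is the share of the untreated loss that depends on the patient's own gain. Two-sided 5% test of the interaction; power in % for gain SD 8/10/12:

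| k | Continuous T20 | Cut at 35 | Cut, with T20 score as covariate |
|---|---|---|---|
| 1 (full relapse) | above 99 | above about 92 | not tabulated |
| 0.5 | 71/89/96 | 41/59/71 | about 50/73/86 |
| 0.35 | 42/61/75 | 21/31/42 | about 27/43/56 |
| 0 (no modification) | about 5 | about 5 | not tabulated |

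A covariate recovers part of the loss. The remaining 10-21 points or so come from cutting the interaction term itself.

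**5. Sensitivity.** With residual SD 10.2 (step 1), gain mean 6.7-12 and gain SD 8-10.2, power is about 50-73% continuous against 30-46% cut when half the gain wears off, and 96-100% against 81-96% when all of it does.

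**6. The opposite truth.** If the effect steps by 6.7 points exactly at 35, the continuous interaction has about 51-53% power, and the cut with T20 and baseline as covariates about 68-71%.

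**The case against.** The strongest defence is that the split asks a legitimate clinical question. The cutoff is fixed in advance, is the entry criterion, separates severe fatigue from the normal range, and is part of the improvement definition. Booster content covers both relapse prevention and coping with normal fatigue, so patients on either side may use it differently. A linear slope answers a somewhat different question, and if the effect really steps at 35 the split does better. This stands, and it is why the contrast should be kept rather than dropped.

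It is also fair that the hypothesis is stated for groups. The patient-level version is an inference, and strictly its modifier is T0 minus T20, not T20 alone. That is a reason to include T0 in the model. The larger power gaps need partial dependence, which the article does not state; under its literal full-relapse assumption little is lost.

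A reader might infer more than the document supports:

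- That over a third of the information is certainly lost. This holds for an unbounded normal score but not for flat or bimodal ones.
- That this analysis decides who will be offered boosters. The article attaches no decision to it.
- That no continuous analysis is planned. The same section announces further moderator analyses and leaves their variables and scale open.
- That the cut makes the test invalid. Type I error stays at about 5%.

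Leaving model details to a separate analysis plan is no fault. Here, however, the article does state the two-group contrast, so the point concerns a choice made and not an omission.

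**Conclusion.** The point holds in a limited form. The planned contrast dichotomises a complete 8-56 score at 35. If modification is graded, that costs roughly 18-37% of the information for the bounded shapes tried, and 36% or more for an unbounded normal score. Under the simulated inputs with error SD 8, interaction power falls from 71-96% to 41-71% at half dependence and from 42-75% to 21-42% at 35% dependence. Keeping the T20 score as a covariate beside the cut narrows the gap but does not close it. Under full relapse both forms exceed about 92% at that error SD, though the cut can drop to 81% with residual SD 10.2. With a true step at 35 the continuous form has no advantage.

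Baseline mean and SD, gain SD, error SD and k are all assumptions. The primary RCT 2 comparison at T52 and its sample size do not depend on this analysis. It is an improvement worth making to a secondary analysis, not a threat to the trial's main conclusion.

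**What to change.** In the section on booster effectiveness at 52 weeks, specify the interaction of condition with the continuous T20 CIS20r fatigue score as the main test of differential effect. The T52 model would contain condition, T20 score, T0 score and condition × T20 score, with a quadratic or spline term as a check on linearity. Report the estimated booster effect with its 95% CI along the T20 score, for example at 25, 35 and 45. Keep the contrast of below 35 against 35 or above as the accompanying clinical presentation, fitted with the continuous T20 score as a covariate.

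The cost is a sentence or two of analysis wording, with no extra data or patients. The downsides are an assumed linear interaction, which the check addresses, and a result slightly less simple to present than two subgroups.

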## Discussion

A study protocol was presented of two RCTs combined in one study. First, non-inferiority will be tested of MS Fit (blended CBT) on fatigue severity compared with face-to-face CBT in severely fatigued patients with MS [13, 16]. Subsequently, superiority will be tested of MS Stay Fit, i.e., additional internet-based booster sessions following MS Fit or face-to-face CBT, compared with no booster sessions on fatigue severity up to 1 year after randomisation.

By combining two RCTs, this study is able to address two important research questions. The non-inferiority trial aims to give more insight in whether the CBT protocol applied in a blended form is non-inferior as to when applied face-to-face. If MS Fit is indeed non-inferior to face-to-face CBT, it probably will be a more time-efficient but also a more accessible treatment option, enhancing implementation of this intervention. Since long-term effects of CBT vary between studies with some showing considerable fatigue relapse [20] and since little is known about the underlying mechanisms of fatigue relapses after successful treatment [7], testing the effect of booster sessions and testing possible mediators and moderators of the response to treatment may contribute to a better understanding of these mechanisms and, most importantly, improving long-term effects. To the best of our knowledge, this is the first study testing the effectiveness of booster sessions in treating chronic severe fatigue. In addition, by training psychologists of 12 participating rehabilitation centres and hospitals, this study aids in implementation of CBT for MS-related fatigue in the Netherlands and Belgium, making effective fatigue treatment more accessible to patients with MS.

In this trial, inclusion criteria and the face-to-face CBT protocol used are similar as in the TREFAMS-CBT study. However, in our study, more rehabilitation centres are including and treating patients, and, even with the same set of enrolment criteria, this may lead to a more varied patient sample. Given the number of therapists (currently 20 therapists are involved) in the study, it is also plausible that there is more variance in therapist-related factors (e.g., familiarity with providing e-health interventions such as blended CBT). Providing an extensive manual, intensive training and supervision of all therapies intends to limit these variants and optimize treatment integrity as much as possible [68], respecting the consistency rules of non-inferiority trials [26, 27]. Taking this into account, these aspects may also well increase generalizability of the results of this pragmatic trial to clinical practice. In addition, in this trial, treatment duration is set at 20 weeks instead of 16 weeks since this is expected to increase opportunities for patients to reach treatment goals and cognitive and behavioural changes.

Non-inferiority of blended CBT is measured by means of fatigue severity as the primary outcome measure, but benefits of treatment may regard other aspects as well (e.g., accessibility, time-efficiency or adherence). Being effective but having a high dropout rate, for example, can also have implications for implementation. These factors will be measured and might help in interpreting the primary trial results.

Even though the content of treatment is similar in both treatments, differences in form of treatment may affect several factors possibly influencing effectiveness. It is known that factors in the therapy relationship (e.g., outcome expectations and working alliance) can contribute to treatment outcome in general [40] but also more specifically in treating fatigue [62]. In general, working alliance is found to be related to self-efficacy, outcome expectancies, treatment adherence and satisfaction [41]. Since in the blended-CBT group therapist contact is more distant and less frequent, this might influence treatment adherence, satisfaction and outcome effects. For that reason, patients’ evaluation of the working alliance, treatment satisfaction and usability of the platform will be taken into account in secondary trial analyses. Outcome expectations are also measured at baseline, but at the time of measurement, patients will not be randomly assigned yet, so these expectations will not apply to the form of treatment that they will adhere to. It could be argued that treatment expectations may be higher in the present study than in the TREFAMS-CBT study since CBT for MS-related fatigue is proven effective now.

In conclusion, this paper presents the study protocol of two combined RCTs testing non-inferiority of blended CBT compared with face-to-face CBT for MS-related fatigue, and the effect of booster sessions on long-term outcome. This study aims to provide more insight in effectiveness of CBT in various applied forms, and in possibilities for improving long-term effectiveness of the treatment. In addition, by conducting the study and training of psychologists in 12 rehabilitation centres in the Netherlands and Belgium, this study is a first step in implementation of CBT in clinical practice.

### Trial status

Patient recruitment started in April 2018 and is expected to end in March 2021. At the time of submission, 64 patients have been randomly assigned. The trial is being conducted in accordance with the protocol version 7, dated 4 July 2019.

## Data Availability

Any request to share the data of these RCTs will be considered by the trial steering committee and will need to be approved by the ethics committee of the Amsterdam University Medical Centers, VU University Medical Center, before granted. An informed consent form in Dutch is available as a supplement.

## Abbreviations

CBT: Cognitive behavioural therapy
CI: Confidence interval
CIRS: Cumulative Illness Rating Scale
CIS20r: Checklist Individual Strength
eCRF: Electronic case report file
EDSS: Expanded Disability Status Scale
FSS: Fatigue Severity Scale
ICF: Informed consent form
ITT: Intention-to-treat
MS: Multiple sclerosis
RCT: Randomized clinical trial
SAE: Serious adverse event
SIP: Sickness Impact Profile
TREFAMS: TREating FAtigue in MS
VPT: Visual Probe Task
WSAS: Work and Social Adjustment Scale
